## Discussion

HL is characterized by its intractable nature and frequent recurrence. The risk factors associated with stone recurrence were reported to be liver atrophy, bile duct stricture, dilatation, residual stones and SOL [2]. This study aimed to demonstrate which drainage method (Roux-en-Y HJ or T-tube drainage) is better for reducing biliary complications in HL patients with SOL.

In 1887, Ruggero Oddi, an Italian anatomist, first proposed the concept of the duodenal papillary sphincter, which was later confirmed and named the SO. The SO is a muscular structure surrounding the confluence of the distal common bile duct and the pancreatic duct into the ampulla of Vater. The main function of the SO is to regulate bile flow into the duodenum and prevent duodenal reflux. With SOL, the SO will undoubtedly lose its one-way “gate” function, which can cause severe bile-intestinal reflux and biliary tract infection [10]. For patients with normal SO function, the best biliary drainage is T-tube drainage. T-tube drainage is relatively simple and has a high stone clearance rate. Because this method retains SO function, it also retains the integrity and continuity of the extrahepatic bile duct structure. T-tube drainage can significantly reduce the incidence of postoperative reflux cholangitis in patients with normal SO function. For patients with complete loss function or SO stenosis, Roux-en-Y HJ is currently one of the best biliary drainage methods [10]. The advantage of Roux-en-Y HJ is that it reduces the reflux of duodenal fluid, but this operation abandoned the Oddi sphincter. The results of a retrospective study showed that Roux-en-Y HJ can significantly reduce the incidence of postoperative cholangitis and recurrence of stones in patients with SO dysfunction [11–13].

There is no consensus on which drainage method is better for HL patients with SOL, and there are no prospective randomized controlled studies that have evaluated the effects of different drainage methods. The biliary drainage method is chosen arbitrarily and is mostly based on the surgeon’s habits. When performing bile duct exploration during surgery, most surgeons often judge the function of the sphincter with a manometry probe or catheter and determine which biliary drainage method is needed. These methods are mostly empirical, lack scientific evaluation and cannot accurately reflect the true function of the SO. This study design features methods and evaluation criteria to evaluate the SO function during the operation. In this prospective randomized controlled study, the patients will be divided into the HJ group and the T-tube drainage group. The postoperative follow-up is standardized. Through statistical analysis of the results of the two groups, a systematic evaluation can be performed to recommend the best surgical method for HL patients with SOL. We believe that the results of this trial will significantly contribute to the evidence on which biliary drainage method is better for HL patients with SOL.

## Trial status

The study protocol was completed in December 2019. Enrolment started on 1 February 2020. The study will continue until sufficient power is reached, approximately until December 2026. Protocol version n.3, January 2020.

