### Number of patients needed

The sample size is based on a two-sided *t* test for differences with respect to the primary parameter and the primary analysis. In a retrospective analysis of our own series, the incidence of biliary complications was 30% in patients with HL with SOL undergoing T-tube drainage. The calculated sample size was 186 (93 per group), with 80% statistical power to detect a difference in the supposed incidence of biliary complications of 15% (30% in the T-tube drainage group versus 15% in the Roux-en-Y HJ group). Given an estimated withdrawal rate of 10%, the minimum required sample size would be 204 patients. We plan to enrol a total of 210 patients (105 per group).

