### Data management and quality assurance

The principal investigators and data analysts will have access to the final cleaned dataset. All paper forms will be scanned and stored at the password cabinet in the First Affiliated Hospital of Anhui Medical University office of clinical trials. All electronic data will be coded and stored separately without the personal data in on a password-protected computer. The files of the participants will be stored for a minimum of 10 years after the end of the study. All relevant information for each subject should be recorded in the case report form (CRF) and inputted into the Microsoft Access database in a timely, truthful and precise manner by trained research staff. An explanation should be given for all missing data. Complete CRF pages will be checked by the principal investigator and the responsible monitor with respect to completeness and plausibility. The patients will also be informed of the outpatient follow-up interviews by telephone, and all items will be regularly accordingly assessed to the schedule shown in Fig. 2. Changes to the database can only be made with joint written consent from the data managers, statisticians and clinical research leaders. The results will be submitted for publication in peer-reviewed journals.

To ensure the safety and validity of the trial, the data will be overseen by an independent Data Safety Monitoring Board (DSMB) for efficacy outcomes and safety, which consists of surgical experts, statistics experts and ethics experts. It is independent from the sponsor and competing interests. During the trial, the DSMB is charged with providing advice recommendations that include (a) continuation of the study, (b) continuation with modification and (c) termination of the study.

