### Statistical analysis

The two-sided null hypothesis for the primary outcome measure states that both study interventions lead to a similar rate of stone recurrence; the alternative hypothesis is that one intervention will perform better than the other. The continuous variables will be recorded as the mean ± SD (for normally distributed variables) or medians and interquartile ranges (for skewed parameters) and will be statistically analysed with Student’s *t* test and the non-parametric Mann-Whitney *U* test, respectively.

Categorical data will be presented as frequencies and group percentages and compared with Fisher’s exact test. Graded data, including age, quality of life and Clavien-Dindo classification, will be compared with the Wilcoxon signed-rank test.

The odds ratio for having biliary complications will be determined with a logistic regression model. The homogeneity of the two groups will be described by comparing the demographic data and the baseline values.

All analyses will be performed on an intention-to-treat (ITT) basis. Statistical Package for the Social Sciences (SPSS) 10.0 (SPSS Inc., Chicago, IL, USA) will be used for statistical analysis. Statistical significance will be defined as *P* < 0.05.

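### The open-ended end-of-study sentence does not match the fixed enrolment of 210, and under the stated two-sided test the two rules lead to different trial sizes

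*Protocol article*

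**What the plan says.** The protocol article describes the end of the trial in two ways.

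- **Number of patients needed** gives a fixed size: "The calculated sample size was 186 (93 per group"), raised to 204 for 10% withdrawal, and then "We plan to enrol a total of 210 patients (105 per group"). The abstract repeats 210. The basis is "with 80% statistical power to detect a difference in the supposed incidence of biliary complications of 15" percentage points, namely "30% in the T-tube drainage group versus 15% in the Roux-en-Y HJ group", and the test is two-sided ("The sample size is based on a two-sided" *t* test).
- **Trial status** gives an open-ended criterion: "The study will continue until sufficient power is reached, approximately until December 2026". Study design adds only that the trial is expected to end in 2026.

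Two other sections bear on the point. Under Statistical analysis there is one threshold: "Statistical significance will be defined as" P < 0.05. Under Data management and quality assurance, "the data will be overseen by an independent Data Safety Monitoring Board (DSMB) for efficacy outcomes and safety", and the board may recommend continuing, modifying or terminating the study. The article states no interim efficacy test, no re-estimation of sample size and no rule for extension.

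**The concern.** An end rule should tell the reader when recruitment stops and when the primary analysis is done. A target of 210 does that. A criterion of sufficient power does not, because the article does not say which power, at which rates, judged by whom or on what data.

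The looseness would be harmless if 210 were the size that gives 80% power. If 210 falls short, anyone who rechecks power during the trial can cite the status sentence to go on recruiting. Depending on what that person has seen by then, the final test at P < 0.05 may or may not keep its nominal error rate, and a reader of the results could not tell which.

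**Working it through.** **Inputs.** From Number of patients needed: p1 = 0.30, p2 = 0.15, difference d = 0.15, 80% power, two-sided test, 93 per group calculated, 105 per group planned, 10% withdrawal. From Statistical analysis: α = 0.05. Allocation is 1:1 (Randomization and blinding). Normal quantiles: 1.960 (two-sided 0.05), 1.645 (one-sided 0.05), 0.842 (80% power).

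**1. The plan's own figure.** With unpooled variance, n per arm = (zα + zβ)² × [p1(1−p1) + p2(1−p2)] / d². The bracket is 0.21 + 0.1275 = 0.3375, and 0.3375 / 0.0225 = 15.

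- Two-sided: (1.960 + 0.842)² × 15 = 117.7, so 118 per arm.
- One-sided: (1.645 + 0.842)² × 15 = 92.7, so 93 per arm.

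Other two-sided formulas give 121 (pooled variance), 119 (arcsine), 122 (*t* test with common SD) and 134 (continuity-corrected). None gives 93. The stated 93 reproduces with a one-sided 5% test, not with the stated two-sided one.

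**2. Power delivered, two-sided 0.05.** With pooled variance under the null, power = Φ{[d√n − 1.960 × √(2 × 0.225 × 0.775)] / √0.3375}. The constant is 1.960 × 0.5906 = 1.1575, and √0.3375 = 0.5809.

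- n = 93: (1.4465 − 1.1575) / 0.5809 = 0.498, power 69%.
- n = 105: (1.5370 − 1.1575) / 0.5809 = 0.653, power 74%.

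| Per arm | Pooled | Unpooled | Fisher's exact |
|---|---|---|---|
| 93 | 69% | 70% | 64% |
| 94 (210 × 0.9 = 189, halved and rounded down) | 70% | 71% | 64% |
| 105 (no withdrawal) | 74% | 75% | 70% |

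Fisher's exact test is shown because Statistical analysis names it for categorical data.

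**3. Size needed for 80%.** 2 × 118 = 236 to 2 × 121 = 242 evaluable patients. Dividing by 0.9 gives 263 to 269 enrolled. Stopping at 210 and continuing to 80% power are therefore different trials under the stated two-sided test.

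**4. What an extension could do to the type I error (assumed scenario).** Suppose the 210 are analysed unblinded, a result with |Z1| ≤ 1.96 triggers extension to N, and all data are retested at 0.05. Under the null, Z2 = √(210/N) × Z1 + √(1 − 210/N) × e, with e an independent standard normal. From 1,000,000 simulated pairs, the chance that |Z1| or |Z2| exceeds 1.96 is:

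| Extended to | Type I error |
|---|---|
| 242 | 6.7% |
| 270 | 7.2% |
| 420 | 8.3% |

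These figures are for a normal test of exact 5% size. Fisher's exact test at 105 per arm has a size of about 3.5% at a common rate of 22.5%, so with that test the inflation would start from a lower base. If the decision is made blind to arm, or from the planning rates alone, there is no material inflation.

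**The case against.** The strongest reply is that the status sentence is a one-line note meaning only that the trial runs until its powered sample has been recruited and followed. Power at fixed planning rates depends on the number of patients, not on the observed difference, so the sentence need not imply a look at the data. The calendar fits: enrolment began on 1 February 2020, follow-up is at least 3 years, and an end in December 2026 puts the last entry at about December 2023. At that date only patients from roughly the first ten months would have complete 3-year outcomes, a thin basis for a data-driven extension. The statisticians are also to be blinded to allocation during data collection and analysis.

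Most of this stands as an account of what was probably meant. It does not make the sentence harmless, because that reading needs 210 to be the powered sample, and under the stated two-sided test it is not.

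A reader might also infer that the board's access to efficacy data, combined with an unadjusted P < 0.05, already breaks type I error control. Two to five equally spaced unadjusted looks would give 8.3% to 14.2%. The article does not support this. It states no interim efficacy test and no number of looks, and review by a monitoring board spends no alpha in itself. Any boundaries may sit in the full protocol, analysis plan or board charter, which are not shown, so their absence from the article is no finding.

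**Conclusion.** The point holds as a defect of wording with a real consequence for trial size. The article gives an open-ended end rule beside a fixed enrolment. At the planning rates and two-sided 0.05 they diverge: 210 enrolled gives about 74% power with no withdrawal and about 70% with 10% withdrawal, while 80% needs 236 to 242 evaluable patients. The two rules agree only under a one-sided 5% test, which the article does not claim to use.

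Loss of type I error control is not shown. The 6.7% to 8.3% range rests on an assumed unblinded look at 210, an extension after a non-significant result, and an unadjusted retest. The documents describe none of these steps. The wording merely fails to exclude them.

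**What to change.** Replace the sentence in Trial status with:

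> Enrolment stops when 210 patients have been randomised; the single primary analysis takes place after the last patient's 3-year visit.

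In Number of patients needed, restate the power as what 210 provides at 30% versus 15% with a two-sided 0.05 test: about 74% if all are evaluable, about 70% if 10% withdraw (pooled normal approximation; lower with Fisher's exact test). Without this second change, the fixed 210 would still stand beside an 80% claim that it does not meet.

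The cost is a few lines of text. The sponsor gives up an informal option to extend and has to state openly that power is below 80%.

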## Data Availability

Datasets used or analyzed in the current study may be provided upon reasonable request of the corresponding author.

## Abbreviations

HL: Hepatolithiasis
SOL: Sphincter of Oddi laxity
HJ: Hepaticojejunostomy
SO: Sphincter of Oddi
CRF: Case report form
